## Abstract

**Background:**

Stroke survivors often exhibit low motivation for rehabilitation, hindering their ability to effectively complete rehabilitation training task effectively and participate in daily activities actively. Reward strategies have been identified as an effective method for boosting rehabilitation motivation, but their long-term efficacy remains uncertain. Transcranial direct current stimulation (tDCS) has been recognized as a technique that facilitates plastic changes and functional reorganization of cortical areas. Particularly, tDCS can improve the functional connectivity between brain regions associated with goal-directed behavior when applied to the left dorsolateral prefrontal cortex (dlPFC). Combing reward strategies with tDCS (RStDCS) has been shown to motivate healthy individuals to exert more effort in task performance. However, research exploring the combined and sustained effects of these strategies on rehabilitation motivation in stroke survivors is lacking.

**Methods and design:**

Eighty-seven stroke survivors with low motivation and upper extremity dysfunction will be randomized to receive either conventional treatment, RS treatment, or RStDCS treatment. The RStDCS group will receive reward strategies combined with anodal tDCS stimulation of the left dlPFC. The RS group will receive reward strategies combined with sham stimulation. The conventional group will receive conventional treatment combined with sham stimulation. tDCS stimulation is performed over 3 weeks of hospitalization, 20 min/time, five times a week. Reward strategies refers to personalized active exercise programs for patients during hospitalization and at home. Patients can voluntarily choose tasks for active exercise and self-report to the therapist so as to punch a card for points and exchange gifts. The conventional group will receive home rehabilitation instructions prior to discharge. Rehabilitation motivation, measured using RMS. RMS, FMA, FIM, and ICF activity and social engagement scale will be compared at baseline, 3 weeks, 6 weeks, and 3 months post-enrollment to evaluate patients’ multifaceted health condition based on the ICF framework.

**Discussion:**

This study integrates knowledge from social cognitive science, economic behavioral science, and other relevant fields. We utilize straightforward and feasible reward strategies, combined with neuromodulation technology, to jointly improve patients’ rehabilitation motivation. Behavioral observations and various assessment tools will be used to monitor patients’ rehabilitation motivation and multifaceted health condition according to the ICF framework. The aim is to provide a preliminary exploration path for professionals to develop comprehensive strategies for improving patient rehabilitation motivation and facilitating a complete “hospital—home—society” rehabilitation process.

**Clinical trial registration:**

https://www.chictr.org.cn/showproj.aspx?proj=182589, ChiCTR2300069068

## 1. Introduction

Half of stroke survivors experiences upper limb (UL) functional impairment, which significantly disrupts daily life (1). However, recovery of upper limb function can continue over an extended period with possibility of improvement even after 6 months post-stroke (2). Evidence suggests a positive correlation between therapy dosage and functional recovery (3), emphasizing the importance of encouraging patients to engage in longer and more frequent sessions (4). Yet, the shortage of rehabilitation resources and high cost of medical treatment mean that most patients do not receive adequate supervised therapy during their hospital stay, let alone after returning home (5). Enhancing patients’ motivation for rehabilitation is crucial to maximize the efficiency of rehabilitation training and utilization of rehabilitation services (6). Thus, researchers are increasingly studying how to motivate patients to actively engage in unsupervised rehabilitation exercises both in hospital and at home (7).

Post-stroke apathy is a significant contributor to low motivation in stroke patients (8, 9). Affecting approximately one-third of stroke patients, apathy symptoms can emerge as early as 4 days post-stroke and persist in most patients up to 1 year after the event, with only a small proportion improving over time (10, 11). Apathy manifests as a gradual decline in rehabilitation motivation with a corresponding decrease or refusal to participate in exercises, thereby reducing the exercise dosage (12, 13). If a patient’s rehabilitation motivation remains low, even the most robust medical resources may prove ineffective. On the contrary, when the rehabilitation motivation is boosted, patients can make constructive self-judgment, actively engage in rehabilitation training, face challenge confidently, and enhance motor relearning (14–17).

Six months post-stroke, apathy may not only psychogenic, driven by psychological and social factors, but also organic, resulting from neurobiological changes (18). The possible neural mechanism underlying this apathy is impairment of the brain network related to goal directed behavior (GDB) (19), which includes the anterior cingulate cortex (ACC) and the nucleus accumbens (NAcc) (9, 20). Another plausible explanation is that infarction may cause functional disruption in the connective area following an acute stroke (21).

Current strategies to enhance patients’ motivation primarily aim to boost decision-making abilities and motor relearning capacity. Approaches to promote the decision-making include motivational interviewing (22, 23), integrating individualized rehabilitation programs based on goal orientation and self-management (24–27) and interventions developed from behavioral economics (28, 29). These methods are based on social cognition theory (30) and self-determination theory (31). Education, coaching, and co-setting goals can enhance patients’ self-efficacy, fostering internal motivation for recovery (32).

Methods to bolster motivation and thus motor relearning include sensor technology (33, 34), robot-assisted technology, and virtual reality equipment (35). These methods promote motor motivation by providing refined feedback. As an intrinsic reward, it enhance patients’ ability to analyze and process feedback, improving motor accuracy, proficiency, speed, and coordination (36). However, it is important to note that stroke survivors’ brain exhibit reduced activation of reward systems associated with motivation and motor learning compared to healthy individuals. Thus, even with these strategies, the effect on motivation improvement may not be significant (37). More potent stimulation or treatment may be needed to normalize reward processing (38). Non-invasive neuromodulation techniques like transcranial direct current stimulation (tDCS) and transcranial magnetic stimulation (TMS) can normalize the activation of motivation-related brain regions in stroke patients (37, 39). Some evidence suggests that TMS or tDCS can alleviate apathy and alter the balance of activity in prefrontal and subcortical areas to encourage successful self-regulation in patients (40, 41).

Despite the existence of various interventions to stimulate patients’ motivation toward recovery, improvements are necessary. First, most approaches focus only on patients’ motivation during treatment, with little attention given to the maintenance of motivation post-treatment (42). Yet, the maintenance of high motivation is most critical for patients with chronic disease, as it directly influences their propensity to initiate unsupervised exercise. Second, the cost-effectiveness, healthcare resource consumption, treatment frequency, availability, acceptability, and generalizability of all current motivational interventions need to be examined and enhanced. Third, there is a lack of interventions targeting secondary alterations in stroke, such as functional decline in brain areas associated with motivation and the associated dysfunctional brain network connections. Future efforts should consider combining motivational interventions from multidisciplinary sources. Last but not least, a comprehensive approach to assessing motivation in stroke patients is lacking. A standardized process for evaluating rehabilitation motivation should be established.

Given this content, our team has designed a simple and resource-efficient treatment plan involving a reward strategy combined with a neuromodulation treatment. We aim to modulate patients’ brain neural activity via tDCS, enhancing the functional connectivity of brain regions linked to goal-directed behavior and the reward system. In addition, we plan to collaborate with patients to set treatment goals and offer external rewards to acknowledge their autonomy and self-drive in completing exercises. This approach aims to stimulate their intrinsic motivation and maintain the initiative of the rehabilitation program throughout the “hospital, home, and society” continuum.

### 1.1. Objectives

This randomized controlled trial intends to evaluate the effectiveness of reward strategies combined with tDCS (RStDCS) in improving rehabilitation motivation in 87 patients with chronic stroke (onset over 6 months), compared to RS group without tDCS and conventional treatment group. Through this pilot study, we aim to verify whether reward strategies designed to boost rehabilitation motivation can provide a feasible approach throughout the entire “hospital, home and society” rehabilitation process. The primary objective is to compare the scores of rehabilitation motivation scale and the frequency of patients participating in unsupervised exercises at baseline, 3 weeks, 6 weeks after treatment, and at a 3-month follow-up. The secondary objective is to evaluate the structure and function, activities, and participation of patients within the framework of ICF to observe whether reward strategies can improve rehabilitation motivation, motor ability, daily living ability, and quality of life through self-reporting and assessment instruments.

## 2. Methods and analysis

### 2.1. Study design

The reward strategy combined with tDCS treatment (RStDCS) for improvement of rehabilitation motivation after stroke study is a randomized, single blind, controlled clinical trial. Subjects will be randomly assigned to either the RStDCS group, the reward strategy with sham tDCS treatment group (RS group), or the conventional treatment with sham tDCS treatment (Control group). All patients will receive either true or sham tDCS stimulation and will be provided with an exercise program manual (content varies based on different requirements). Evaluators and statisticians will remain blind to the subjects’ group assignments. Assessments will be conducted at 0, 3, and 6 weeks and followed up at 3 months using assessment scales and behavioral observations. Prior to the assessment, the evaluator will be trained. Assessment scales include the Rehabilitation Motivation Scale (RMS), Fugl-Meyer Assessment Scale (FMA), Function Independent Measure (FIM), and ICF Activity and Participation Scale (ICF). Table 1 shows the schedule of enrollment, interventions, and assessments.

**Table 1 tab1:** The schedule of enrolment, interventions, and assessments.

	Study period				
	Enrolment	Allocation	Post-allocation		Close-out
Timepoint**	*−1 day*	0 day	*3 weeks*	*6 weeks*	*3 months*
Enrolment:					
Eligibility screen	X				
Informed consent	X				
Allocation		X			
Interventions:					
Group A (RStDCS)					
Group B (RS + sham)					
Group C (Conventional + sham)					
Assessments:					
RMS		X	X	X	X
FMAS		X	X	X	X
FIM		X	X	X	X
ICF		X	X	X	X

### 2.2. Study population and recruitment

Initial steps are described in Figure 1. Participants (total of 87) will be recruited from the inpatient and outpatient departments of the Rehabilitation Medicine Center of Yueyang Hospital of Integrated Traditional Chinese and Western Medicine affiliated to Shanghai University of Traditional Chinese Medicine. Patients with confirmed upper limb or hand dysfunction after stroke will be screened for eligibility to participate in this study based on the criteria. Once a patient has been assessed as eligible by the rehabilitation physician, they will receive initial study information. After a minimum 2 weeks of consideration, patients are invited to meet with the research physician to discuss any remaining questions and sign the informed consent.

**Figure 1 fig1:**
[figure not shown]
Flowchart of study design.

### 2.3. Inclusion and exclusion criteria

Eligible patients should meet the following criteria:

Able to provide written informed consent and understand study’s content, follow-up requirements and are willing to complete questionnaires and provide the necessary information at follow-up visits.Diagnosed with stroke based on the diagnostic criteria for ischemic stroke set by the National Cerebrovascular Academic Conference in 2014.Age 18–70 years, no gender limitation, right-handed.No cognitive impairment or communication impairment, Mini-Mental State Test (MMSE) score of ≥ 27 (43).First stroke onset with the course of disease lasting more than 6 months，less than 3 years.Upper limb and hand dysfunction, Brunnstrom Stage ranged from I to VI.Patients’ rehabilitation motivation scale score of ≤25.

The exclusion criteria of this study are:

Serious systemic diseases such as cardiopulmonary diseases that would prevent them from tolerating rehabilitation treatment.(History of) Psychosis, major depression (including suicidal tendencies) or epilepsy, HAMD−17 scores>24 (44).Presence of severe systemic diseases such as diabetes and uremia.Severe joint contracture.Any form of consciousness disturbance (somnolence, confusion, stupor, coma, and delirium, etc.) due to any cause, Glasgow coma score < 15 (45).Contraindications for tDCS according to safety guidelines, such as implanted metal foreign bodies or other electronic devices.Auditory or visual impairment may affect assessment and treatment.Use of drugs that alter the excitability of the cerebral cortex (like antiepileptic drugs, sedatives, and hypnotics, etc.).Severe pain, sleep disturbance, or mental disorder.

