### 2.4. Randomization and allocation

Patients are randomized into three groups using a random number table, with allocation via sequentially numbered, opaque, sealed envelopes. Upon determining the eligibility of the subjects, the envelopes are opened in sequence and the subjects are assigned to the corresponding test group.

The researcher generating and preserving the random sequences is separated from the trial and will have no clinical involvement. Neither the subjects nor their routine care therapists will be aware of the group assignments.

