**Figure 2 fig2:**
[figure not shown]
Groups overview and research implementation process.

In contrast, the RS group undergoes upper extremity rehabilitation with reward strategies and sham tDCS stimulation, identical in position to the RStDCS group. The current is ramped up and then immediately ramped down in the sham condition in 60 s to mimic the perception of current onset.

Reward strategies involve offering extrinsic rewards in recognition of patients’ independent performance encouraging sustained active rehabilitation motivation. Specifically, a 21-day inpatient-training manual is developed for chronic stroke patient with upper limbs dysfunction and low motivation. Upon discharge, a 21-day home training program is customized for each patient. Figure 3 shows the schematic diagram of reward strategy self-monitor brochure in in-patient and out-patient settings. Both program are tailored according to the Brunnstrom stage of upper limbs and hands, passive range of motion (PROM), muscle tone, muscle strength, fine motor abilities, grip strength, and activities of daily living (ADL). They incorporate exercises to improve and maintain joint mobility, therapeutic exercises, functional training, and ADL training. The Supplementary File 3 shows the contents of the library of active exercise program.

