#### 2.6.2. Secondary outcome measures

The FMA, created by Swedish doctor Fugl-Meyer on the basis of Brunnstrom rating Scale in 1980. It is a widely recognized and frequently used, with proven reliability and validity (47). FMA can help to monitor and measure the level of ICF structure and function in patients. The FIM, proposed by researchers from the Functional Assessment Research Center of New York State in 1987, assesses the ADL ability of stroke patients comprehensively and objectively (48). The ICF Activity and Participation Scale appraises the health status and health-related condition over the past 30 days covering six areas: understanding and communication, physical activity, self-care, interpersonal interactions, life activity, and social participation. Both FIM and ICF Activity and Participation can measure the level of ICF Activity and Participation level.

Behavioral observation data included the number of therapist-supervised active exercise sessions during hospitalization and the number of self-reported active exercise sessions by patients at home. After 42 days of reward training, the researchers collect the program manual and tally the number of completed sessions.

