#### 2.8.2. Statistical analyses

SPSS 26.0 version will be used for data analysis. Chi-square tests are used to compare count data, and descriptive statistical analyses is conducted to study the basic information of subjects in RStDCS group, RS group, and control group. Independent sample *t* tests will be used for intergroup comparisons of measurement data following a normal distribution, while paired sample *t* tests will be used for intragroup comparisons, represented as “(
$\bar{x}$
±s).” If the data do not follow a normal distribution, independent sample rank sum tests will be used for intergroup comparisons, and paired sample rank sum tests for intragroup comparisons, represented as [M (P25, P75)]. To investigate the impact of using reward strategies combined with neuromodulation techniques on upper limb dysfunction in chronic stroke survivors with low motivation over time, a repeated measure ANOVA will be performed, with rehabilitation motivation, motor function, functional independence, ICF activity, and participation as dependent variables. The model includes three groups (RStDCS group, RS group, and control group) and three test types (0, 3, and 6 weeks). Due to the strict requirements for repeated measurement data, missing cannot occur. If a sample lacks measurement data, all the data from that sample will be excluded from the model during analysis. A value of *p* less than 0.05, two-tailed, is considered statistically significant.

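### Exercise-session counts for RStDCS versus RS are compared without adjustment for motor severity at entry, which may cost precision and leaves chance imbalance uncorrected

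*Protocol article*

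**What the plan says.** All places are in the protocol article.

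- **Eligibility (2.3):** "Upper limb and hand dysfunction, Brunnstrom Stage ranged from I to VI". The range covers every stage, so it restricts nothing.
- **Intervention (2.5):** for the inpatient and home reward programmes, "Both program are tailored according to the Brunnstrom stage of upper limbs and hands", among other features.
- **Allocation (2.4):** "Patients are randomized into three groups using a random number table", with sealed envelopes. No stratification factor is named.
- **Behavioural outcome (2.6.2):** supervised active sessions in hospital and "the number of self-reported active exercise sessions by patients at home". The total is obtained once, when the 42-day reward period has ended: "the researchers collect the program manual and tally the number of completed sessions". This section lists the counts as secondary, while section 1.1 puts exercise frequency in the primary objective and speaks of it at baseline.
- **Between-group tests (2.8.2):** "Independent sample *t* tests will be used for intergroup comparisons of measurement data following a normal distribution", with rank-sum tests otherwise.
- **Longitudinal model (2.8.2):** a repeated-measures ANOVA is fitted to the scales, "with rehabilitation motivation, motor function, functional independence, ICF activity, and participation as dependent variables"; session counts are not listed there. Its only terms are arm (three levels) and visit (weeks 0, 3 and 6), and no covariate is named.

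**The concern.** RStDCS versus RS is the comparison that isolates tDCS, because both arms receive rewards and differ only in true or sham stimulation. Session counts are its behavioural measure. A patient with little voluntary movement may complete fewer active sessions than one near full recovery, whatever their motivation, and the trial admits both.

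The scales have a week-0 value that takes up much of this spread. The counts have none in section 2.6.2 and fall outside the ANOVA, so the remaining listed tests are all that applies to them, and none of those carries a covariate. If motor stage affects the counts, its share of the variance stays in the error term. A chance difference in stage between two arms of about 29 then passes uncorrected into the estimated effect.

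**Working it through.** **1. The plan's own figure.** Section 2.8.1 gives f = 0.25, α = 0.05, power 0.90, correlation 0.5, nonsphericity 0.5 and N = 72. With 3 groups and 3 visits, λ = f²·N·m·ε/(1−ρ) = 0.0625 × 72 × 3 × 0.5 / 0.5 = 13.5. The degrees of freedom are (3−1)(3−1)(0.5) = 2 and (72−3)(3−1)(0.5) = 69. The noncentral F gives power 0.906, so 72 reproduces. Per arm, 24/0.85 = 28.2, rounded up to 29, which makes 87. This figure is not in dispute. It concerns the ANOVA interaction, and session counts are not in that model.

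**2. Chance imbalance, RStDCS versus RS.** Assumption: 50% of patients are in stages I-III (the article gives no stage mix). The quantity is the probability that the two arms' shares differ by at least 20 points.

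- 87 patients allocated without restriction: about 13%.
- 29 per arm (a gap of 6 or more patients, since 0.20 × 29 = 5.8): about 15%.
- 24 completers per arm (a gap of 5 or more, since 0.20 × 24 = 4.8): about 19%.
- If the share is 30% instead: about 11% at 29 per arm and 15-16% at 24.

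**3. Precision on session counts.** If stage explains a fraction R² of count variance, adjustment multiplies the residual SD by √(1−R²). A difference of d then acts as d/√(1−R²), and the equivalent gain in sample is 1/(1−R²). Assumptions: d = 0.6 SD and R² = 10-30%; the test is a two-sided 5% two-sample t test.

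| R² | d/√(1−R²) | 1/(1−R²) | Power, 29 per arm | Power, 24 per arm |
|---|---|---|---|---|
| 0 | 0.60 | 1.00 | 0.61 | 0.53 |
| 0.10 | 0.63 | 1.11 | 0.66 | 0.57 |
| 0.20 | 0.67 | 1.25 | 0.71 | 0.62 |
| 0.30 | 0.72 | 1.43 | 0.77 | 0.68 |

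The 24-per-arm column matches the number the plan expects to keep after dropout.

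**4. FMA, FIM and RMS.** Week 0 is a level of the ANOVA, so the group-by-visit interaction works on change from baseline. If stage has the same correlation s with baseline and follow-up scores of equal SD, its covariance with the change is proportional to s − s = 0, and a stable severity difference cancels.

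If baseline FMA (correlation ρ with follow-up) is adjusted for, the further share of variance that stage removes is [s(1−ρ)]² / [(1−ρ²)(1−s²)]. At an assumed s = 0.7:

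- ρ = 0.9: 0.07² / (0.19 × 0.51) = 5%
- ρ = 0.8: 0.14² / (0.36 × 0.51) = 11%
- ρ = 0.5: 0.35² / (0.75 × 0.51) = 32%

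The unadjusted tests of scores at each visit do not have this protection. Adjusting for the baseline score leaves 1−ρ² of the variance: 0.75, 0.36 or 0.19 at ρ = 0.5, 0.8 or 0.9.

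**The case against.** **Simple randomisation with unadjusted tests is valid.** This stands. The significance level already allows for chance imbalance, so the issue is efficiency and how well one realised comparison can be read. A reader might infer that the tDCS comparison is biased; the documents do not support that.

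**Tailoring may weaken the link between stage and counts.** This stands in part. Programmes fitted to stage, free choice of tasks (section 2.5) and targets meant to be achievable (section 3) could make completion similar across stages. Nothing in the article shows that stage drives the count, which is why R² is an assumption.

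**The counts may have a baseline.** Section 1.1 speaks of exercise frequency at baseline, and sections 2.1 and 2.6 schedule behavioural observation from week 0. Section 2.6.2, where the outcome is defined, describes only a tally from a manual used during treatment. The passages pull in different directions, so the absence of a baseline count cannot be called certain.

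**Motor outcomes are already protected.** This largely stands. A reader might infer that FMA and FIM carry the full noise of severity. In the ANOVA interaction they do not, and section 2.6.2 describes the FMA as built on the Brunnstrom scale, so a close severity measure is already among the repeated measurements.

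**Allocation should be stratified.** A reader might infer this from section 2.4. The article's silence on strata is weak evidence, and under section 2.9.2 a mid-trial change would need prior ethics approval. It is not pursued here.

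**Stage may not be recorded for analysis.** The baseline list in section 2.6 does not name it and ends open. For the two rewarded arms, however, it must be known in order to tailor the programme, and baseline FMA is scheduled in Table 1 for everyone.

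**Conclusion.** The point holds in a limited form. The stated analysis of session counts uses no measure of motor severity, although every stage is eligible and the reward programmes depend on stage. The consequence is possible loss of precision and exposure to chance imbalance in RStDCS versus RS, with no bias on average.

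The size is moderate and conditional. A severity gap of 20 points or more between these arms has a probability of about 13-15% at 29 per arm and about 19% at 24 completers. Adjustment would add roughly 4 to 15 percentage points of power for a 0.6 SD difference. These figures rest on an assumed 50% share in stages I-III, an assumed R² of 10-30% and an assumed effect of 0.6 SD. They show what adjustment buys if stage matters, not that it does. For FMA, FIM and RMS the exposure is confined to the unadjusted between-group tests at each visit.

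**What to change.** In section 2.8.2:

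1. Analyse session counts for RStDCS versus RS by regression or ANCOVA with one prespecified severity covariate measured at entry: upper-limb Brunnstrom stage (ordinal, or I-III versus IV-VI) or baseline FMA. Name the upper-limb stage explicitly, because section 2.5 refers to stages of both upper limb and hand.
2. Adjust the per-visit between-group comparisons of FMA, FIM and RMS for the baseline value of the same score.

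Fixing the covariate now also prevents its being chosen after an imbalance is seen. The cost is a sentence or two of text and one or two degrees of freedom. Baseline FMA needs no new data collection; entry stage needs none provided it is entered in the case report form. If stage proves unrelated to the counts, almost nothing is lost. Allocation and eligibility stay as they are.
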